### 9.3 Serious Adverse Events

A **serious adverse event** (SAE) is defined as follows:

Any adverse experience that results in any of the following outcomes:

- death
- life-threatening situation (subject is at immediate risk of death)
- in-patient hospitalisation or prolongation of existing hospitalisation (excluding those for study therapy or placement of an indwelling catheter, unless associated with other serious events)
- persistent or significant disability/incapacity
- congenital anomaly/birth defect in the offspring of a subject who received study product
- other: Important medical events that may not result in death, be immediately life-threatening, or require hospitalisation, may be considered a SAE when, based upon appropriate medical judgment, they may jeopardise the subject and may require medical or surgical intervention to prevent one of the outcomes listed in this definition. Examples of such events are:
  - intensive treatment in an emergency room or at home for allergic bronchospasm
  - blood dyscrasias or convulsions that do not result in hospitalisation
  - development of drug dependency or drug abuse.

#### 9.3.1 Clarification of Serious Adverse Events

Death is an outcome of an AE, and not an AE in itself. In reports of death due to "Disease Progression", where no other information is provided, the death will be assumed to have resulted from progression of the disease being treated with the study product(s).

All deaths in the following periods, regardless of cause, must be reported to MDL:

- deaths of subjects on study
- deaths occurring within 30 days of last study product dose or within 30 days of last study evaluation, whichever is longer.

“Life-threatening” means that the subject was at immediate risk of death from the event as it occurred. This does not include an event that might have led to death, if it had occurred with greater severity.

Complications that occur during hospitalisations are AEs. If a complication prolongs hospitalisation, it is a SAE.

“In-patient hospitalisation” means the subject has been formally admitted to a hospital for medical reasons, for any length of time. This may or may not be overnight. It does not include presentation and care within an emergency department.

The Investigator should attempt to establish a diagnosis of the event based on signs, symptoms and/or other clinical information. In such cases, the diagnosis and not the individual signs/symptoms should be documented as the AE and/or SAE.

### **9.3.2 Serious adverse event reporting requirements**

#### **9.3.2.1 All serious adverse events**

MDL has requirements for expedited reporting of SAE’s meeting specific requirements to worldwide regulatory authorities; therefore, all appropriate parties must be notified immediately regarding any SAE that occurs after the first dose of study product has been administered. The procedures for reporting all SAEs, regardless of causal relationship, are as follows:

- complete the “Serious Adverse Event Report” CRF page
  - fax the SAE report to the SAE hotline within 24 hours of the Investigator’s knowledge of the event at [contact]
  - for fatal or life-threatening events, also fax copies of hospital case reports, autopsy reports, and other documents when requested and applicable.

The Sponsor may request additional information from the Investigator to ensure the timely completion of accurate safety reports.

The Investigator must take all therapeutic measures necessary for resolution of the SAE. Any medications necessary for treatment of the SAE must be recorded in the concomitant medication section of the subject’s CRF.

#### **9.3.2.2 Investigator reporting requirements for serious adverse events**

An SAE may qualify for reporting to regulatory authorities if the SAE is considered to have a possible causal relationship to the study product and is unexpected/unlisted based upon the current IB. In this case, all Investigators will receive a formal notification describing the SAE.

Where this is required by local regulatory authorities, and in accordance with the local institutional policy, the Investigator should notify (in writing) the Independent Ethics Committee (IEC) of SAEs as soon as is practical.

### **9.4 Follow up of Serious and Non-serious Adverse Events**

Follow-up of serious and non-serious AEs will continue through the last day on study (including the follow-up, off study medication period of the study), until the Investigator and/or the Sponsor determine that the subject’s condition is chronic or stable, or up to 30 days after the last dose of IMP, whichever is longer. The Sponsor may request that certain AEs be followed until resolution.

## **9.5 Clinical Laboratory Abnormalities and Other Abnormal Assessments as Adverse Events or Serious Adverse Events**

All laboratory values must be reviewed in real time by the Investigator. Given that all laboratory data are collected and statistically analysed according to their respective toxicity gradings, laboratory abnormalities that occur without related clinical symptoms and signs should generally not be recorded as adverse events. Where possible, the overall diagnosis rather than the laboratory abnormality should be recorded on the AE page of the CRF. This will avoid duplication of laboratory abnormalities in both the AE and laboratory reports. Abnormal laboratory results that are of clinical significance may be reported as AEs and should be reviewed with the Medical Monitor.

Any laboratory test result that meets the criteria for a SAE (refer to Section 9.3) should be recorded as an AE, the AE page of the CRF completed and a SAE form also completed in order for the Sponsor to collect additional information about that abnormality, including information regarding relationship to study product or other causes, any action taken and resolution.

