#### 9.2.1 Assessment of Adverse Events

All AEs will be assessed by the Investigator and recorded on the appropriate CRF page, including the date of onset and resolution, severity, relationship to study product, outcome, action taken with study medication, and seriousness.

Severity should be recorded and graded according to the AIDS Clinical Trial Group (ACTG) grading scale (see Appendix A) or, if there are no specific toxicity grades for the parameter, the grading in Table 4 used.

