## **9.6 Guidance for toxicity management**

AEs and abnormal laboratory values will be graded according to the Toxicity Grading Scale (Appendix A). IMP will be interrupted or discontinued due to toxicity according to the toxicity grading scale.

All abnormal values should be confirmed by repeat testing within 3 calendar days of receipt of results prior to dose adjustment or interruption, unless such a delay is not consistent with good medical practice. For the purpose of monitoring toxicities, the baseline value is defined as the last value prior to the administration of the first dose of study medication. The value must be obtained from the central laboratory. All assessments of toxicity will be based on changes from this value, regardless of later interruptions to dose.

The following table (Table 5) outlines the procedure for temporary or permanent IMP discontinuation due to an AE or SAE. All subjects who experience a study product related AE should be followed until resolution of the AE, even if the subject has interrupted or discontinued study product.

Table 5: Toxicity management.

| Clinical or laboratory* abnormality                                | Action Taken                                     |                                                                                           |
|--------------------------------------------------------------------|--------------------------------------------------|-------------------------------------------------------------------------------------------|
|                                                                    | Continue dosing at Investigator discretion       | Permanently discontinue dosing                                                            |
| Grade 1                                                            | Regardless of causality                          | N/A                                                                                       |
| Grade 2                                                            | Regardless of causality                          | N/A                                                                                       |
| Grade 3
Lab events of clinical significance*
Clinical Events | Unrelated to treatment
Unrelated to treatment | Unknown or at least possibly related
Unknown or at least possibly related # |

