## 10 DATA SAFETY MONITORING BOARD REVIEW

The Sponsor has convened a DSMB that is charged with the review of this study. The DSMB review will occur as soon as practical after the W4 dose administration of IMP is complete for each cohort and will include all available safety data.

Each DSMB meeting will have an open session and an optional closed session. Open session review materials will be blinded and include aggregate data on study accrual, baseline characteristics and general study progress, and will be made available to the DSMB, Sponsor representatives, and invited guests (e.g. participating Investigators) to facilitate a general discussion of study progress. Attendance at the closed session will be restricted to DSMB members and those individuals who were directly involved in the preparation of the review materials. The DSMB will review available safety results of the trial and logistical issues such as accrual, retention, quality of clinical and laboratory data, and safety and implications of results of external studies. Unblinding envelopes will be made available to the DSMB should unblinding be requested.

The DSMB will make its recommendation to the Sponsor about dose escalation, halting or termination of the clinical trial. At each meeting the DSMB will review all available safety data and the DSMB will recommend to the Sponsor to:

- proceed with dose escalation
- pause enrolment pending either resolution of specific issues or amendment of the protocol as specified
- pause enrolment and all scheduled trial administrations pending either resolution of specific issues or amendment of the protocol as specified
- terminate the study

The DSMB, following a meeting to review the data, may recommend to the Sponsor and Principal Investigator not to permit further dose escalation if any of the following conditions are met:

- a subject experiences a SAE regarded as “probably” or “definitely” related to Opal-HIV-Gag(c) (i.e unblinded review of the event)
- any three subjects experience a similar severe adverse event (with a toxicity of at least grade 3) which is “probably” or “definitely” related to Opal-HIV-Gag(c) (i.e. unblinded review of the events)
- the Principal Investigator, DSMB and/or the Sponsor feel that consideration by the DSMB of a full interim safety summary is warranted following detection of a pattern of repeated or unresolved clinical AEs or laboratory abnormalities.

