### 12.2 Sample Size Determination

Twenty seven subjects will be included in the study, which is within the recommended 20 to 80 subjects for a Phase I study (see Chow and Liu 2004, FDA general considerations for the clinical evaluation of drugs 1997).

A possible safety signal will be indicated by three or more subjects with toxicity of at least grade 3 considered to be related to treatment among the 18 patients randomised to receive Opal-HIV-Gag(c) immunotherapy. If the true rate of severe treatment related toxicities is 5% or 10%, then the probability of three or more events being reported is 5.8% and 26.6% respectively. If the true rate of severe treatment related toxicity is greater than 20% and 30%, then the probability of three or more events being reported is greater than 72.9% and 94.0% respectively.

In the 18 Opal-HIV-Gag(c) subjects, a 95% confidence interval will be calculated around the observed rate of severe treatment related toxicities. If one, two or three events are observed among the 18 Opal-HIV-Gag(c) subjects, then the calculated 95% confidence intervals will be (0.1 to 27.3%), (1.4 to 34.7%) and (3.6 to 41.4%) respectively. A total of 18 Opal-HIV-Gag(c) subjects will give at least reasonable power to detect severe treatment related toxicities at rates of 20% or greater.

By including placebo recipients, laboratory assays assessing the immunogenicity of the HIV immunotherapy are subjected to more rigorous testing for validity and specificity. The inclusion of a placebo group with double blinding may also assist in reducing the potential for volunteers to make assumptions about the candidate material they are receiving and subsequent changes of behaviour.

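### The protocol does not require a recorded causality rating for symptom-free Grade 3–4 laboratory abnormalities, so related ones can be missed by the 3-of-18 safety signal

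*Protocol*

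**What the plan says.** **What goes on the AE page.** Protocol Section 9.5 sets the default: "laboratory abnormalities that occur without related clinical symptoms and signs should generally not be recorded as adverse events". The reason it gives is that laboratory data are analysed by toxicity grade anyway and should not be duplicated. It leaves two routes to the AE page. One is optional: "Abnormal laboratory results that are of clinical significance may be reported as AEs and should be reviewed with the Medical Monitor". The other is an instruction: "Any laboratory test result that meets the criteria for a SAE (refer to Section 9.3) should be recorded as an AE", with an SAE form that also collects relationship to study product.

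**Where causality is recorded.** Section 9.2.1 says: "All AEs will be assessed by the Investigator and recorded on the appropriate CRF page". The causal relationship is one of the items to be entered there. No other routine place for relationship is named.

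**What uses causality.**
- Section 12.2 defines a possible safety signal as "three or more subjects with toxicity of at least grade 3 considered to be related to treatment" among the 18 subjects randomised to active treatment. It also plans a 95% interval for the rate of severe treatment-related toxicity.
- Section 10 has two three-subject rules, one on dose escalation and one on halting. Both contain "any three subjects experience a similar severe adverse event (with a toxicity of at least grade 3", followed by an attribution condition.
- Table 5 in Section 9.6 has Grade 3 and Grade 4 rows for "Lab events of clinical significance", and the action on dosing depends on relatedness.

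**How the data are tabulated.** AEs are to be presented by severity and relationship (Section 12.6.4.1). Laboratory parameters are to be summarised by time point, toxicity grade and dose level, with no mention of relationship (Section 12.6.4.2).

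**The concern.** The headline safety measure needs two facts for each subject: a toxicity of Grade 3 or higher, and a judgement that it is related to treatment. For a symptom-free laboratory abnormality the first is always available from the laboratory data. The second is assured only if the event reaches the AE page, and 9.5 steers it away from there. The duplication that 9.5 avoids therefore removes the one field that the laboratory data lack.

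Haematology and clinical chemistry are part of the primary safety evaluation (Section 12.4.1), and in a first-in-human study a raised transaminase or lipase, or a fall in neutrophils or platelets, may well come without symptoms. If such findings go unrated, the estimated rate of related severe toxicity is too low and the signal is less likely to be raised than 12.2 states. An SAP cannot repair this, because a causality rating that was never collected cannot be derived later.

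**Working it through.** **1. Can a related laboratory toxicity go uncounted?** Take a confirmed Grade 3 laboratory value without symptoms that the investigator would judge related.
- Under 9.5 it is by default not an AE.
- If judged clinically significant, it may be reported, but need not be. The protocol gives neither a grade threshold nor a definition of clinical significance for this.
- An isolated symptom-free value need not meet any SAE criterion in Section 9.3, so the mandatory route may not apply.
- If it is clinically significant, Table 5 calls for a relatedness judgement, but no form is required to hold it.
- Section 11.4 puts an abnormal laboratory result on the AE page when it is the reason for removal from the study. Section 11.3, however, aims to keep subjects who stop dosing in the study, so this does not close the gap.

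The grade will be in the laboratory tables, while the relationship may be recorded nowhere.

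**2. Reproduce the plan's figures.** With X ~ Binomial(18, p),

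P(X ≥ 3) = 1 − (1−p)^18 − 18p(1−p)^17 − 153p²(1−p)^16.

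At p = 0.20: 1 − 0.0180 − 0.0811 − 0.1723 = 0.729 (unrounded 0.7287). The other rates in 12.2 also reproduce: 5.8% at 5%, 26.6% at 10% and 94.0% at 30%. So do the exact (Clopper-Pearson) intervals for 1, 2 and 3 events of 18: 0.1–27.3%, 1.4–34.7% and 3.6–41.4%.

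The arithmetic is right. It takes the true rate to be the rate that reaches the count, so it assumes that every related Grade 3+ toxicity is rated.

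**3. Let a share f of affected subjects go unrated.** The countable rate becomes p(1 − f). The documents give no value for f, so the table shows an assumed range.

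| True rate p | f | Countable rate p(1 − f) | P(X ≥ 3) |
|---|---|---|---|
| 20% | 0 | 20% | 72.9% |
| 20% | 25% | 15% | 52.0% |
| 20% | 50% | 10% | 26.6% |
| 20% | 75% | 5% | 5.8% |
| 30% | 0 | 30% | 94.0% |
| 30% | 25% | 22.5% | 80.5% |
| 30% | 50% | 15% | 52.0% |
| 30% | 75% | 7.5% | 14.8% |

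**4. Effect on the interval.** Suppose three of 18 subjects have a related Grade 3+ toxicity and one of the three is an unrated laboratory event. The observed rate drops from 3/18 = 16.7% to 2/18 = 11.1%, the interval moves from 3.6–41.4% to 1.4–34.7%, and the signal threshold is not reached.

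**The case against.** A reader might infer that laboratory toxicities are barred from the AE form, never receive a causality judgement and are invisible to the DSMB. The documents do not support that.
- Section 9.5 states a general default, not a ban. It offers Medical Monitor review and optional reporting, and it directs results meeting SAE criteria to the AE page and the SAE form.
- Table 5 requires a relatedness judgement for clinically significant Grade 3 and 4 laboratory events. The gap is in recording that judgement.
- Section 12.2 counts toxicities, not AEs, and Section 9.6 grades laboratory values and AEs on one scale. The signal rule does not itself exclude laboratory events. They fall out only where a rating is missing.
- Under Section 10 the DSMB reviews all available safety data at each meeting, and one escalation criterion names a pattern of laboratory abnormalities without requiring AE status or a causality rating. Only the three-subject rules worded in terms of adverse events are exposed.

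It can also be said that the CRF is not shown and may hold a relationship field elsewhere, that all laboratory data will be listed and tabulated by grade and dose level in a placebo-controlled trial, and that 12.2 describes only a possible signal within a descriptive analysis. These points limit the harm: a cluster of laboratory toxicities would probably be noticed. They do not close the gap. The protocol fixes when an AE page is completed and names no other routine place for the rating. The laboratory-pattern criterion is a judgement without a count, and the signal and its interval depend on relatedness.

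**Conclusion.** The point holds as a gap in required recording. For symptom-free Grade 3–4 laboratory abnormalities that do not meet SAE criteria, the protocol does not require a recorded causality rating. Related ones left off the AE page can be missed by the 12.2 signal, by its 95% interval and by the three-subject rules in Section 10. Sections 9.5 and 9.6 also pull apart: one makes AE reporting of these events optional, while the other makes an action depend on their relatedness.

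The size cannot be fixed from the documents. At a true rate of 20%, the stated 72.9% falls to 52.0% if a quarter of affected subjects go unrated and to 26.6% if half do. These figures assume that the unrated events are not reported by either optional route and that the subjects concerned have no other countable Grade 3+ event. They show how sensitive the operating characteristics are and do not predict the loss. If every such event is rated, the figures in 12.2 stand as written.

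**What to change.** 1. **Section 9.5:** require relationship to study product to be recorded, on the AE page or in a laboratory CRF field, for every confirmed Grade 3 or 4 laboratory abnormality that is worse than the pre-first-dose value, with or without symptoms. Section 9.6 already defines that baseline and Table 5 already asks for confirmation by repeat testing. Keep the no-duplication rule for Grades 1 and 2.
2. **Section 12.2:** state that these events, when rated as related, count in the three-or-more signal and in the 95% interval.
3. **Sections 9.5, 9.6 and 10:** reconcile the AE-recording rule with Table 5 and with the adverse-event wording of the three-subject rules, so that it is clear whether a rated laboratory toxicity falls under them. What the dosing, escalation and halting rules should be is for the sponsor and the DSMB, and nothing is proposed here.

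The cost is protocol wording, CRF completion guidance, a few extra CRF entries, and a footnote where an event appears in both the AE and the laboratory tables.

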## **9.6 Guidance for toxicity management**

AEs and abnormal laboratory values will be graded according to the Toxicity Grading Scale (Appendix A). IMP will be interrupted or discontinued due to toxicity according to the toxicity grading scale.

All abnormal values should be confirmed by repeat testing within 3 calendar days of receipt of results prior to dose adjustment or interruption, unless such a delay is not consistent with good medical practice. For the purpose of monitoring toxicities, the baseline value is defined as the last value prior to the administration of the first dose of study medication. The value must be obtained from the central laboratory. All assessments of toxicity will be based on changes from this value, regardless of later interruptions to dose.

The following table (Table 5) outlines the procedure for temporary or permanent IMP discontinuation due to an AE or SAE. All subjects who experience a study product related AE should be followed until resolution of the AE, even if the subject has interrupted or discontinued study product.

Table 5: Toxicity management.

| Clinical or laboratory* abnormality                                | Action Taken                                     |                                                                                           |
|--------------------------------------------------------------------|--------------------------------------------------|-------------------------------------------------------------------------------------------|
|                                                                    | Continue dosing at Investigator discretion       | Permanently discontinue dosing                                                            |
| Grade 1                                                            | Regardless of causality                          | N/A                                                                                       |
| Grade 2                                                            | Regardless of causality                          | N/A                                                                                       |
| Grade 3
Lab events of clinical significance*
Clinical Events | Unrelated to treatment
Unrelated to treatment | Unknown or at least possibly related
Unknown or at least possibly related # |
| Grade 4
Lab events of clinical significance*
Clinical Events | Unrelated to treatment
Unrelated to treatment | Unknown or at least possibly related
Unknown or at least possibly related              |

\* All grade 3 or 4 laboratory abnormalities must be confirmed by repeat testing as soon as possible, preferably within 24 hours of receipt of results prior to dose interruption or discontinuation, unless such a delay is not consistent with good medical practice.

#The Investigator may continue dosing at their discretion for transient and self limiting events that may be attributed to IMP but are expected for a vaccine (such as fever): these grade 3 event(s) must be followed to resolution ( $\leq$  grade 2) before the subject is discharged from the clinic.

